### Study design

The TRIGGER study is designed as a non-blinded two-arm multi-centre randomised controlled superiority trial with parallel-groups and equal randomisation (1:1). This study protocol is reported following the SPIRIT guideline for standard protocol items in interventional trials [22]. The information on the mHealth intervention is reported following the mHealth evidence reporting and assessment (mERA) checklist [23].

### Ethics and trial registration

The Medical Research Ethics Committee of the University Medical Center Utrecht has approved the study protocol (protocol number: NL53125.041.15, issued October 2015, issue date amendment: May 2016 (reason: additional recruitment in secondary care)). The trial is registered in the Dutch trial register (trial-ID: NTR5515). Important protocol modifications will be communicated with the Medical Research Ethics Committee and the trial register.

### Setting

The study will be conducted in general practices and hospitals across the Netherlands, starting from December 2015 onwards. In the Netherlands, approximately 85% of all T2DM patients are treated in primary care. Practice nurses conduct the regular monitoring visits two to four times yearly. Once a year, the monitoring visit is conducted by, or together with, the general practitioner (GP), but when necessary more often. Patients are referred to hospital based internists/endocrinologists when adequate glycaemic control cannot be achieved or when other problems occur that are beyond the scope of the GP. The internists/endocrinologists closely collaborate with specialised diabetes nurses [2]. All participating sites can be found at the trial website [24]. Participating hospitals are (in alphabetical order): Bethesda Diabetes Research Center, HagaZiekenhuis, Meander Medical Center, Röpcke-Zweers Ziekenhuis and Ziekenhuis Gelderse Vallei.

### Participants

Eligible participants are T2DM patients aged 40–70 years, treated for their diabetes by the recruiting health care provider, sufficiently fluent in Dutch, on insulin treatment since at least three months, and with HbA1c > 53 mmol/mol (> 7%) at most recent measurement. Logistic requirements are the possession of an email address and a smartphone. In the Netherlands, 96% of the population has access to a personal computer [25]. In 2016, 89.6% of the population between 45 and 65 years old had access to a mobile phone with internet capacity, while among those above 65 years only 50.9% had access [26]. We used age as an inclusion criterion because we expect the probability for patients > 70 years to possess a smartphone to be lower than in the younger patient group and besides, for many patients aged > 70 years a less stringent glycaemic target is recommended according to the Dutch Primary Care Guidelines [2]. Patients are excluded when they have a history of alcoholism, drug abuse, dementia or a major psychiatric disorder that is likely to invalidate informed consent or limit the ability of the individual to comply with the protocol requirements.

### Recruitment

Most general practices are recruited via diabetes care groups. These care groups organise and coordinate the diabetes care programme, and are responsible for the delivery of diabetes care [27]. Care groups in the Netherlands are similar to Accountable Care Organizations in the USA and Clinical Commission Groups in the UK [27]. We expect that about 40 general practices and five small to medium sized hospitals are needed to enrol the required number of 228 participants (see Fig. 1 and ‘Sample size’ below). When a general practice or a hospital consents to participate, the researchers will instruct the practice nurse or diabetes nurse. Afterwards the practice nurse, diabetes nurse, GP or hospital data manager selects the patients based on a query in the electronic medical record, the practice nurse or the diabetes nurse conducts the informed consent procedure and performs the data collection.

**Fig. 1 Fig1:**
[figure not shown]
Participant flowchart with the expected number of patients

### Randomisation

Simple, fixed block randomisation will be generated at the patient level. Randomisation will be performed centrally using a web-based computerised random-number generator provided by an independent contractor (Research Online, https://random.mendixcloud.com/login.html) at the research centre. For general practices, the coordinating researcher will generate the allocation sequence, in the order in which patients are enrolled, and forwards this information to the company that developed the software for the smartphone app. Ten days after the patient has provided written informed consent, the practice nurse will inquire after the randomisation outcome and will inform the patient about it, and on how to use the paper patient diary. The patient receives an email with regard to the steps to be taken to receive the app-messages and on how to complete the online questionnaires. For the hospitals, the coordinating researcher will forward the randomisation outcome directly to the patient 10 days after the patient has provided written informed consent.

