### Concealment of allocation and blinding

The study is not blinded at patient level because of the nature of the intervention, which requires overt participation. The practice nurses/diabetes nurses/outcome assessors are also not blinded to patient allocation.

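### Randomisation is called both simple and fixed block, concealment from the coordinating researcher is not established, and chance imbalance in care setting is left uncontrolled

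*Protocol article*

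**What the plan says.** The Randomisation section of the protocol article names the method in one line: "Simple, fixed block randomisation will be generated at the patient level". It gives no block size and no stratification factor.

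On who produces the sequence, it first says: "Randomisation will be performed centrally using a web-based computerised random-number generator provided by an independent contractor". For general practices it then says that "the coordinating researcher will generate the allocation sequence, in the order in which patients are enrolled", and that this role passes the result to the app developer. For hospitals it says only that "the coordinating researcher will forward the randomisation outcome directly to the patient 10 days after the patient has provided written informed consent"; who generates the allocation there is not stated. In general practices disclosure runs through the nurse: "Ten days after the patient has provided written informed consent, the practice nurse will inquire after the randomisation outcome".

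The section headed Concealment of allocation and blinding deals with blinding alone. Patients know their arm, and "The practice nurses/diabetes nurses/outcome assessors are also not blinded to patient allocation".

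On care setting, the Ethics and trial registration section records a May 2016 amendment for "additional recruitment in secondary care". The Setting section explains that "Patients are referred to hospital based internists/endocrinologists when adequate glycaemic control cannot be achieved", or for other problems outside the GP's remit. The Analysis section adjusts for the baseline value, age, sex, diabetes duration and insulin dose. Care setting is not in that list.

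**The concern.** Simple randomisation cannot be predicted but does not force equal arms. Fixed blocks force balance but become predictable towards the end of each block. A reader cannot tell which one produced the 1:1 allocation.

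The choice matters more here because the trial is open and its outcome assessors are unblinded. Concealment of the next assignment is then the main protection against selection at entry. The text gives a study-team member a hand in the sequence and does not say that the next assignment is hidden from that role, or that it is released only once the patient can no longer be withdrawn from entry.

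Setting is a separate, smaller matter. By the article's own account, referral to hospital is related to poor glycaemic control, so setting may be prognostic for HbA1c. It is known before randomisation, yet the plan controls it neither by design nor in the model.

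**Working it through.** **1. The plan's own figure.** The Sample size section gives a difference of 0.41, SD 1.1, 80% power and 5% significance (two-sided assumed). The normal approximation gives n per arm = 2 × (1.960 + 0.842)² × 1.1² / 0.41² ≈ 113. The t-test version gives 113.96, so 114 per arm and 228 in total. The stated figure reproduces, and nothing below changes it.

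**2. What each reading of the method implies.** Under truly simple randomisation of 228 patients, the probability of exactly 114/114 is 5.3% (binomial), and the 95% range for one arm is 99 to 129. At 99:129, power is 79.7% against 80.3% for equal arms (normal approximation). Simple randomisation would therefore cost almost no power. The two readings differ mainly in predictability.

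**3. Predictability of fixed blocks.** Take a 1:1 block of size 2m, with the size and all earlier allocations known. An assignment is certain once one arm is used up within the block. The expected number of certain positions is 2m/(m+1), so the share is 1/(m+1). For a block of 4 this is 4/3 of 4 positions. Expected correct guesses in a block of 4 are 1/2 + 2/3 + 2/3 + 1 = 2.83, or 71%.

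| Assumed block size | Certain in advance | Best-guess accuracy |
|---|---|---|
| 2 | 50% | 75% |
| 4 | 33% | 71% |
| 6 | 25% | 68% |
| 8 | 20% | 67% |

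The block size is an assumption throughout.

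**4. Who could hold that knowledge.** The Recruitment section gives selection of patients to site staff, and consent to the practice or diabetes nurse. It expects about 40 practices and five hospitals for 228 patients, so 228/45 ≈ 5 per site. If one sequence serves all sites, a nurse sees only fragments of it. The coordinating researcher handles allocations in both settings, so this is the role that could plausibly know every earlier one.

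**5. Chance imbalance in setting.** The hospital share is not given, so 10%, 25% and 50% of 228 are assumed (23, 57 and 114 patients). With 114 per arm, the number K of hospital patients in the intervention arm is hypergeometric, and the gap between arms is |2K − H|/114, where H is the number of hospital patients.

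| Hospital share | SD of gap (points) | P(gap ≥ 10 points) |
|---|---|---|
| 10% | 4.0 | 0.7% |
| 25% | 5.7 | 6.6% |
| 50% | 6.6 | 14.5% |

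For scale, suppose the two settings still differed after adjustment by as much as the planned effect, 0.41. A 10-point gap would then shift the treatment estimate by 0.10 × 0.41 = 0.041. The 0.41 is used here only as a yardstick; the article gives no estimate of a setting effect.

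**The case against.** A reader might infer that staff who recruit patients can foresee the next allocation. The article does not support this. The generator is central and supplied by an independent contractor, and patients are taken in the order of enrolment. Nurses take consent, and the outcome reaches nurse or patient only 10 days later. Blocks run separately by site would make prediction easier, but the text does not say that they are. The coordinating researcher, who might know more, is given no part in selecting or consenting patients. The contractor and researcher statements can also be read together, as the researcher operating the contractor's tool. This objection stands against any claim that entry is open to manipulation, and the percentages above are not a count of entries that could be subverted.

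A reader might also infer that care setting is left unbalanced. It is balanced in expectation; only chance imbalance is uncontrolled. Referral is not solely for poor control. Every patient must be on insulin with HbA1c above 53 mmol/mol, and adjustment for baseline HbA1c, diabetes duration and insulin dose takes up part of any setting effect.

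Block size and the detailed concealment procedure may be in the full protocol, so their absence from an article is not counted here. What remains rests on what the article states: a method described in two incompatible ways, a study-team member generating the general-practice sequence, a concealment heading with no concealment beneath it, and an explicit covariate list without setting.

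**Conclusion.** The point holds in a limited form. The description of the method contradicts itself unless *simple* means *unstratified*. The text also does not establish that upcoming assignments are concealed from the coordinating researcher. If blocks are of constant size, between 20% and 50% of assignments (assumed sizes 8 to 2) would be certain in advance to someone who knows the block size and all earlier allocations. That risk is conditional, falls plausibly on one role, and is reduced by the central generator and by disclosure after consent. No bias in HbA1c is shown or estimated.

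The setting issue is one of avoidable chance imbalance. Its probability depends on a hospital share that the article does not give, and its effect is partly absorbed by baseline HbA1c. Both parts are inexpensive to improve, and neither calls the sample size into question.

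**What to change.** - Name one method in the Randomisation section. If *simple* was meant as *unstratified*, say so.
- For patients still to be randomised, use permuted blocks of randomly varying size, generated and held in the contractor's system. Release each allocation to the coordinating researcher only after the patient is irrevocably entered. State this under Concealment of allocation and blinding.
- Add care setting (general practice or hospital) as a covariate in the adjusted HbA1c model. This can be done for all patients, including those already randomised.
- Stratifying by setting is optional.

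The cost is a small amendment to the randomisation settings and one degree of freedom in the model. Recruitment began in December 2015 and the article appeared in October 2018, so the change of scheme may reach only part of the sample. The corrected description and the covariate are not affected by that timing. N stays at 228.

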### The intervention

Patients randomised to the intervention group will receive app-messages regarding dietary habits, physical activity, prevention of hypoglycaemia, and glucose variability (see Fig. 2). These app messages are clear, unidirectional messages containing specific goals, healthy living challenges, information, or questions (see Table 1 for examples). They are sent in Dutch only. The content of the intervention is determined by reviewing research literature of existing mHealth interventions and is in accordance with (inter-) national guidelines. An independent dietician, physiotherapist and practice nurse reviewed the messages’ content and wording. Afterwards, two T2DM patients on insulin reviewed the messages. Feedback was used for finalisation before the messages were entered into the app software system. Messages are framed grammatically correct, free of textese (“SMS language”), benefit-oriented, polite, nonaggressive and directive [28, 29]. Moreover, the intervention is tailored, according to patient’s preferences (see further). The intervention is free of charge, which is especially important for people with low socio-economic status; which might be a category of patients that needs self-management support but is not well approached by ‘conventional’ educational sessions [30].

**Fig. 2 Fig2:**
[figure not shown]
TRIGGER app home screen. Translation: contact onderzoekers = contact information; informatie studie = study information; instellingen = settings; voeding = nutrition; beweging = physical activity; hypo’s voorkomen = preventing hypoglycaemia; glucose regulatie = glucose regulation

**Table 1 Tab1:** Examples or app messages

Category	Message
Dietary habits	- Fruit juices are not as healthy as many people think: they contain lots of sugar and calories. Try to consume fruit juices as infrequently as possible, eat fruit instead! - Don’t drink any soda today. Choose water, or tea or coffee without any sugar instead.
Physical activity	- Take the stairs instead of the elevator, wherever you are. Or take the elevator to one floor below and take the last stairs. All steps count! - People with a healthy weight are advised to be physically active for at least 30 min a day. People who are overweight are advised to have at least 60 min of physical activity each day.
Prevention of Hypoglycaemia	- Instruct your spouse, family, neighbour, colleague or a friend on how they should act when you have a hypoglycaemic event. - Do you have nocturnal hypoglycaemic events? Ask your doctor whether it is advisable to adjust your insulin dose.
Glucose variability	- Never inject insulin into the tough skin of insulin-induced lumps; because of slower absorption there, this may lead to blood glucose fluctuations. - When you have high blood glucose levels, it is important to drink a lot (1.5–2 l sugar free beverages per day) and to take your medication properly.

Users will receive a push notification to direct them to open the app when a new app-trigger is available. When the app is not opened in the following 24 h, a reminder SMS is sent: the SMS fall-back system. The number of reminder SMSs will be monitored.

The timing of the messages is either at random times between 9.30 a.m. and 8.00 p.m. or at times associated with the content of the message (e.g. messages containing advice for dinner are sent in the morning or early afternoon in order to get the receiver to adapt to that advice). The intervention will be tailored to the patients’ preferences, they can choose on:The topics: hypoglycaemia will be a mandatory topic, it should be combined with at least two of the following topics: dietary habits, physical activity or glucose regulation (including glycaemic variability).The frequency: two or six times per week, one app-trigger per day. The option to prolong the intervention with another 3 months after the first 6 months. During this period the patient will receive app-triggers with unaltered frequency and topics.

Apart from receiving app-triggers, the intervention group will receive usual care for their T2DM.

Patients randomised to the control group receive usual care according to the Dutch primary care guidelines, that advise two to four diabetes monitoring visits per year [2]. Through diabetes education from either the GP or the practice nurse, patients learn about target values for glycaemic control, lipids and blood pressure, a healthy lifestyle, recognising hyperglycaemic or hypoglycaemic episodes and how to respond to these episodes. Patients randomised to the control group are not able to use the smartphone app we developed. To increase the participation rate, patients in the control group will be given the opportunity to use the app after the study has ended.

### Technical details of the smartphone app

The smartphone app is compatible with Android and iOS operating systems. A proprietary personal health record (PHR) platform (“Gezondheidsmeter”, Curavista eHealth) is combined with both Android and iOS smartphone app technology for the end-user. The PHR platform is the host for the push message technology. The push message technology contains the algorithms for timely delivery, logging of end-user opening the message and fall-back SMS. Android and iOS technology is used to create an app for reception and storage (library) of the push messages. The mHealth intervention has no connection or interaction with any national or regional Health Information System. We did not involve end-users in usability testing but tested the technical aspects of the intervention ourselves. The PHR platform is subjected to Dutch privacy laws and has concluded a compliant data processing agreement. The messages do not contain any personal information. The logging data, such as successful delivery of messages, are anonymised by separating them from the personal data.

### Outcomes

The primary study outcome is glycaemic control, defined as the HbA1c level after a follow-up of 6 months in the app-trigger group compared to the control group. As a co-primary outcome we will analyse the percentage of patients who achieve an HbA1c level ≤ 53 mmol/mol (≤7%) without any hypoglycaemic event (plasma glucose < 3.5 mmol/L (< 63 mg/dL)). Secondary outcomes are BMI, body weight, waist circumference, insulin dose, lipid profile, blood pressure, number of hypoglycaemic events, glycaemic variability, self-management, food habits, physical activity, health status, diabetes-dependent quality of life, diabetes treatment satisfaction and satisfaction with the app (intervention group only) after 6 months. Moreover, we will investigate the cost-effectiveness of the intervention after 6 months, and the sustainability of the intervention effect. The latter is investigated in the intervention group only: we will compare the effect of 3 months prolonged use of the app to stopping with the use of the app, on HbA1c, on the percentage of patients who achieve an HbA1c level ≤ 53 mmol/mol (≤7%) without any hypoglycaemic event, BMI, and health status. Prolonged users are individuals from the intervention group who choose to continue the intervention after 6 months (T6); discontinued users are those who do not continue using the app after T6.

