### Sample size

Based on the decrease in HbA1c in previous mHealth studies [9, 10, 18, 21, 31], we expect a mean difference in HbA1c level of 0.41% with a standard deviation of 1.1% between the intervention group and the control group after 6 months. To detect this difference in the primary outcome with an 80% power and a non-significant difference of 5% after 6 months, 228 T2DM patients (114 per treatment group) are needed. We used SAS version 9.4 (SAS Corp., Cary NC) for the sample size calculation.

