### Analysis

Age and sex of our study population will be compared to those who declined to participate to investigate selection (bias). We will also compare baseline characteristics of our study population to those of similar Dutch T2DM patient cohorts.

Intention-to-treat analysis will be performed for the primary and secondary outcomes. If necessary, a multiple imputation technique will be used to handle missing data.

To analyse continuous variables we will use general linear models. Binary outcome variables will be analysed with logistic regression. To analyse the number of hypoglycaemic events we will use a Poisson regression. If necessary, the analysis will be adjusted for overdispersion or underdispersion.

Firstly, we will perform a univariable analysis to examine the intervention effect. Afterwards we will perform a multivariable analysis corrected for the following baseline characteristics: baseline value, age, sex, duration of diabetes and insulin dosage.

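### HbA1c and the target-without-hypoglycaemia composite are both placed at primary level, but the 5% and 80% in the sample size cover HbA1c alone

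*Protocol article*

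**What the plan says.** The Outcomes section of the protocol article opens with "The primary study outcome is glycaemic control, defined as the HbA1c level after a follow-up of 6 months", compared between arms. The next sentence raises a second outcome to the same level: "As a co-primary outcome we will analyse the percentage of patients who achieve an HbA1c level" of 53 mmol/mol or lower with no hypoglycaemic event. The secondary outcomes are listed separately after that. The Abstract uses the same primary and co-primary labels, and the first item under Research questions asks about both outcomes together.

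The Sample size section plans for one of them: "we expect a mean difference in HbA1c level of 0.41% with a standard deviation of 1.1"%. It continues "To detect this difference in the primary outcome with an 80% power and a non-significant difference of 5% after 6 months", and concludes that "228 T2DM patients (114 per treatment group) are needed". It gives no expected rate, difference or power for the composite.

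The Analysis section assigns a model to each type of variable (general linear models for continuous outcomes, logistic regression for binary ones) and says "Intention-to-treat analysis will be performed for the primary and secondary outcomes". The article does not state whether one or both primary-level outcomes must be significant, in what order they are tested, or how the 5% is shared.

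**The concern.** When a trial has two outcomes at primary level, its error rate and power depend on the rule that joins them. If either may support the claim, there are two chances of a false positive. If both are required, there are two chances of missing a real effect. The article sizes one outcome and declares two, so its 5% and 80% may not describe the conclusion the trial will draw.

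The practical risk is a split result, above all a significant HbA1c difference with a non-significant composite. The article does not say whether that counts as success. Patients, nurses and outcome assessors all know the allocation, so a success rule left open could be settled after the results are visible.

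**Working it through.** **Inputs from the Sample size section:** difference 0.41%, SD 1.1%, power 80%, 114 per arm. The 5% is worded as "a non-significant difference of 5% after 6 months" and read here as alpha. Sidedness is not stated.

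**1. Reproducing the stated size.** Normal approximation: n per arm = 2 × (1.960 + 0.842)² × 1.1² / 0.41² = 113.0. The two-sample t-test gives 113.96, so 114 per arm and 228 in total, an exact match, with 80.0% power. A one-sided 5% would give 90 per arm, so the plan used two-sided 5%. The arithmetic is right, and it spends the whole 5% on HbA1c.

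**2. Either outcome suffices, each tested at 5%.**
- Independent tests: 1 − 0.95² = 9.75%.
- Test statistics with correlation 0.5: 9.1%. With correlation 0.8: 7.8%.
- Simulated trials of 114 per arm, with HbA1c normally distributed and the composite derived from it, give about 8.4-9.8%.

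The error rate is therefore about 8-10%.

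**3. Either outcome suffices, alpha split at 0.025 each.** The standard error is 1.1 × √(2/114) = 0.1457, so the expected z is 0.41 / 0.1457 = 2.814. HbA1c power = Φ(2.814 − 2.241) = 71.7%, or 71.1% by t-test. Restoring 80% would need 137 per arm (274) by the normal formula, or 139 per arm (278) by t-test.

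**4. Both must succeed.** The 5% is protected, but joint power can be no greater than HbA1c's 80%. Going further needs composite rates, which the article does not give. The following are assumptions:
- control mean at 6 months 7.6-8.4%, SD 1.1%, and a treatment shift of 0.41%;
- 40-80% of control patients free of hypoglycaemic events;
- composite rate = Φ((7 − mean)/1.1) × event-free share, compared with a two-proportion test at 114 per arm.

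Example with a control mean of 8.0%: Φ(−0.909) = 0.182 in controls. The treated mean is 7.59%, giving Φ(−0.536) = 0.296. With the same event-free share in both arms:

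| Event-free share | Control | Intervention | Composite power |
|---|---|---|---|
| 60% | 0.182 × 0.6 = 10.9% | 0.296 × 0.6 = 17.8% | about 31% |
| 80% | 0.182 × 0.8 = 14.5% | 0.296 × 0.8 = 23.7% | about 42% |

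Over the whole assumed range:

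| Effect on event-free share | Composite power | Power for both |
|---|---|---|
| None | about 19-46% | about 18-44% |
| 10-15 points higher with the app | about 34-82% | no more than the smaller of the composite's power and 80% |

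**5. HbA1c tested first at 5%, composite only if HbA1c is significant.** The error rate stays at 5%, HbA1c power stays at 80% and the total stays at 228.

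**The case against.** The strongest reply is that the text already ranks the outcomes. Outcomes and the Abstract introduce HbA1c in the singular as the primary outcome or endpoint and add the composite afterwards. Sample size speaks of "To detect this difference in the primary outcome with an 80% power", again in the singular. If HbA1c leads, both planning figures hold and the fault is a loose label. This stands in part: it is a fair reading, but it is not written down. The co-primary label and the joint research question point the other way.

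The second reply is that testing order and alpha allocation are commonly left to the full protocol or analysis plan, neither of which is shown. That also stands. A reader might infer that the plan tests both outcomes at 5% with no order, but the Analysis section only names models, and its silence is not such a statement. The list of primary-level outcomes and the basis of the sample size are nevertheless fixed in this article, and they do not match. No unseen document could make 228 patients deliver both the 5% and the 80% for a genuine co-primary pair on these planning values.

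The third reply concerns magnitude. A reader might infer that the composite's power is far below 80% under the plan's own effect. The low figures assume no effect on hypoglycaemia, whereas the Background hypothesises fewer events and The intervention makes hypoglycaemia the mandatory topic. A 10-15 point gain in event-free share is itself an assumption, but it lifts composite power to about 34-82%. The low range should not be quoted alone.

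**Conclusion.** The concern holds in a limited form. The 228 is correct for HbA1c at two-sided 5% and 80% power. It does not support two outcomes of equal primary standing: the error rate rises to about 8-10% if either can win, HbA1c power falls to about 71% if alpha is split, and power is capped at 80% if both are required. These results follow from the article's own figures, plus a range of correlations for the error rate. The composite and joint power ranges rest on assumed means and event-free shares.

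Two stronger conclusions are not supported. One is that the 5% and 80% cannot both be true: they can, if HbA1c is the sole or first-tested primary outcome. The other is that a trial positive on only one outcome cannot be interpreted: an HbA1c effect beside a composite for which no power was planned is still interpretable. What is missing is a stated rule for whether it counts as success. This is a should-fix matter, since sample size and models can stay as they are.

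**What to change.** In the Abstract, Outcomes and Analysis sections:
- name HbA1c at 6 months as the single primary outcome, tested at two-sided 5%;
- make the composite a key secondary outcome, tested at 5% only if HbA1c is significant.

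In Sample size, state that the 80% power applies to HbA1c only and that the trial is not sized for the composite. Update the trial register to match, before results are compared between arms.

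The cost is wording and a registry update, with the total unchanged at 228. The small downside is that the composite cannot carry a confirmatory claim if HbA1c fails. The alternatives cost more. Letting either outcome win with a Bonferroni split needs about 274-278 patients to keep 80% power for HbA1c. Requiring both means stating expected composite rates and sizing the trial for the pair.
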